### Formal data collection

Survey data regarding the primary outcome for both groups, injury incidents, will be collected at baseline and every 3 months throughout the 12-month follow-up time period. In coordination with the local education bureau, the preschools will organize a caregiver-teacher meeting every 3 months. The class teacher will send the online survey link and ask all caregivers to complete the survey at the caregiver-teacher meeting. All primary outcome data will be collected through online survey. If caregivers fail to complete the online questionnaire, the classroom teacher will contact them to collect the survey data.

Collection of secondary outcome data will be carried out at baseline for both groups and after the intervention group completes each safety-related theme course designed for the intervention group. Secondary outcome data will be collected simultaneously from the control group to maintain comparison between two groups, but we will not disseminate any correct answers or teachings to the children in the control group before the study ends to avoid contamination in that group. All secondary outcomes data will be collected via preschoolers playing an evaluation version of the interactive games that has different story plots from the teaching version and permits retention of evaluation results. The evaluation version of the interactive games will not include any modules that disseminate injury prevention information or display evaluation results to children. Administration of the assessment will occur in a quiet environment. Each child will complete the tasks individually in the Safety Experience Room, with other classmates staying in the classroom respectively during the evaluation.

In order to assess children in the control group, relevant hardware and software (the multimedia touchscreen computer with the evaluation version of interactive games installed) will be delivered to control preschools accordingly. Staff members and teachers will help children start and reset the interactive games as well as maintain a quiet evaluation environment during the evaluation process.

Before formal data collection, teachers involved in both groups will learn to operate the evaluation games. Teachers will enter each child’s ID number and supervise individualized data collection but will not communicate with children or see children’s evaluation results. All data will be stored in the game backend database.

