### Interventions

Both the intervention and control groups will receive routine school-based education on safety and injury prevention from their preschool. This education generally encompasses general health knowledge and skills, including injury prevention, and is performed by preschool teachers.

The intervention group will also receive the Safety Experience Room intervention. The Safety Experience Room involves creation of a space designed to teach safety and injury prevention. It can easily be renovated from typical Chinese preschool classrooms according to the standards in Table 1.

**Table 1 Tab1:** General description of the Safety Experience Room intervention design

Item	Requirement

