**I. Infrastructure**	
1. Space	A room with at least 60 square meters
2. Furnishings	(1) 65-inch multimedia computer with touch screen (2) Moveable computer holder (3) Bookshelves (4) Child-sized chairs (5) Office chair and table for instructor (6) Teaching props to simulate traffic environments, including models of pedestrian traffic light, zebra crossing, traffic signs, and vehicles (7) Teaching props to simulate natural water environments, with models of inflatable ball pool (simulated water area), fences, safety warning signs, and lifesaving equipment
3. Accessories	Floor covered by soft mats
4. Functional zones	(1) Multi-media zone (2) Simulated scenario zone (3) Spare zone

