**Fig. 4 Fig4:**
[figure not shown]
Instructional materials of the Safety Experience Room intervention (A. animation videos; B. interactive games; C. large-picture story books)

For the two teaching themes of road traffic injury and drowning, we will utilize teaching props that simulate traffic and natural water environments in the simulated scenario zone. These lessons will convey relevant safety behaviors to children through learning tasks guided by their instructors.

To summarize, the Safety Experience Room offers five important educational aspects to impart safety under the guidance of the instructor (Table 1):

watching animation videos on a multimedia computer with touchscreen;playing interactive games with coherent game plots using the large touchscreen multimedia computer;experiencing scenarios in simulated traffic and natural water environments;reading large-sized picture story books and listening to relevant story recordings related to the learning themes;hearing summaries of the key safety behaviors from the teachers at the end of each course.

Instruction will be conducted over a six-week period, with one theme conveyed each week. To enhance learning among this young group of children, we will expose the children to a similar set of lessons a second time, over the next six weeks. Repetition of lessons should enhance learning and memory, which we expect to translate to safer behaviors outside the classroom [20].

If the Safety Experience Room intervention proves feasible and effective as hypothesized, we will deliver the intervention to children in the control group after completing the entire intervention, and then disseminate it broadly to other rural preschoolers across China.

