**1. Road traffic injury**
a. Pedestrians should use zebra crossings to cross the road
b. Pedestrians should only cross the road when they see a green light
c. Even when accompanied by adults to cross the road, children should look left and right
d. Do not stand or play near parked or moving cars or trucks
e. Do not play near the road
f. Do not run, chase, skip, or jump when crossing the road

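### The knowledge test is placed in a room that control preschools do not have, so the test setting for this secondary outcome differs by arm

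*Protocol article*

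**What the plan says.** The knowledge outcome is measured with an evaluation version of the interactive games, at baseline and after each theme course, at the same times in both arms. On the place of testing, Formal data collection says: "Each child will complete the tasks individually in the Safety Experience Room, with other classmates staying in the classroom respectively during the evaluation". No exception by arm is given.

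For controls, the same section says that "relevant hardware and software (the multimedia touchscreen computer with the evaluation version of interactive games installed) will be delivered to control preschools accordingly". It mentions no room, props or furnishings for them, and requires only that the surroundings be quiet.

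The Interventions section assigns the room to one arm: "The intervention group will also receive the Safety Experience Room intervention". If the programme proves feasible and effective, controls get it later: "we will deliver the intervention to children in the control group after completing the entire intervention".

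Table 1 lists what the room contains, including "Teaching props to simulate traffic environments, including models of pedestrian traffic light, zebra crossing, traffic signs, and vehicles" and "Teaching props to simulate natural water environments, with models of inflatable ball pool (simulated water area), fences, safety warning signs, and lifesaving equipment". It also lists bookshelves and a "Moveable computer holder".

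**The concern.** A between-arm comparison of a test score is clean only if both arms sit the test under the same conditions. Here the protocol fixes a place of testing that one arm does not have. Followed as written, intervention children take every post-lesson test in their teaching room, and controls take it somewhere else in their preschool.

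Two mechanisms could then raise intervention scores beyond what children have learned. Being back in the teaching room may prompt recall that would not come elsewhere. Objects in view may also hint at an answer. Either would mix learning with the effect of the setting. The protocol expects the lessons to carry over to behaviour outside the classroom, and a score taken in the teaching room reflects that less well.

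**Working it through.** The protocol gives no figure to reproduce. The check compares the relevant sections.

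**1. Can the sentence hold in both arms?** The location rule covers every child. Only the intervention arm has the room (Interventions), and controls could get it only after the intervention is complete. For testing they receive the computer and the evaluation games. There are two readings:
- Taken literally for all children, the rule cannot be carried out in control preschools.
- Taken as meant for intervention children only, it leaves the control location unstated beyond being quiet.

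On either reading the setting differs by arm.

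**2. Do the stated safeguards cover the room?** The evaluation game has other storylines than the teaching game, carries no teaching modules and shows no results. Children are tested singly in quiet surroundings, and teachers neither talk to them nor see their scores. These rules protect the instrument and its administration. None deals with the room's contents.

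**3. Which items could a prop cue?** Table 3 (18 items) against the props in Table 1:

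| Theme | Items | Relation to a listed prop |
|---|---|---|
| Road traffic | 6 | 2 direct: 1a ("Pedestrians should use zebra crossings to cross the road") and 1b (crossing on green) |
| Falls | 6 | 0; props are used for road traffic and drowning only |
| Drowning | 6 | about 1 to 3, loosely: 3f (safety floats), 3c (floating rescue objects), possibly 3d (natural water, through fences or warning signs) |

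The direct matches number 2. With the loose ones the count could reach 2 + 3 = 5. This matching is a judgement, because the protocol does not link props to items.

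**4. What share of the score is that?** Assume the 18 items are weighted equally, which the article does not state.
- One item: 1/18 = 5.6%.
- The two direct items: 2/18 = 11.1%.
- All five: 5/18 = 27.8%.

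These are ceilings on exposure and do not estimate bias. To reach one, every intervention child would have to miss the item without the cue and get it right with it. The lower end is 0.

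**5. Baseline and later tests.** At baseline nothing has been taught, so recall prompted by the teaching room cannot operate. A constant visual cue would already be in the baseline score. Recall prompted by the room can arise only after teaching, so adjusting for baseline knowledge would not remove it.

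**The case against.** The best defence is that the article does not describe biased testing. The room measures at least 60 square meters, and its multimedia zone is named separately from the simulated scenario zone that holds the props. The props may be out of sight or put away. The operation manual covers evaluation with the games and may settle the set-up. Knowledge is a secondary outcome scored on the course's own content, and effects outside the room are judged by caregiver-reported injury.

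Much of this stands, and it limits the point. A reader might infer that intervention children are tested beside props that display the right answers. The documents do not support that. No section says the props are in view during testing, and a model crossing or traffic light shows an object but does not state the rule. A reader might also count three or more items as having their answer on show. Only 1a and 1b clearly match a prop. For 3c, nothing shows that the listed lifesaving equipment is the set of common objects meant. Nor can the teaching-room effect be claimed at baseline.

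The defence does not remove the conflict itself. The article states a location for every child that controls cannot use. Silence on how props are handled would be left to the manual, but this is a stated rule.

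**Conclusion.** The point holds as an unstandardised test setting for one secondary outcome, caused by a sentence that cannot be true for control preschools. That controls are tested outside such a room is inferred from their not having one; their actual location is not given. If there is bias it would favour the intervention arm on the knowledge score at the post-lesson tests. Its size cannot be derived from the protocol and may be zero. At most a handful of the 18 items, and none on falls, relate to a listed prop. The primary injury outcome is unaffected. The change is worth making because it is cheap and removes both the contradiction and an avoidable doubt about the knowledge result.

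**What to change.** In Formal data collection, replace the reference to the Safety Experience Room with one rule for both arms: each child is tested individually in a quiet room that contains no safety teaching materials. In intervention preschools the touchscreen can be moved there on its holder. Where no other room is free, allow testing in the Safety Experience Room with props and story books stored or covered, and say so. State the control location in the same terms.

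The cost is minor logistics at each test: moving the computer, or clearing or covering materials. No new equipment is needed if a second room or storage space is available, which the article does not confirm. A short, content-free touchscreen warm-up in both arms is optional and not needed for this fix.

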### Data analysis plan

Primary data analysis will employ an intention-to-treat (ITT) approach. Descriptive statistics will be calculated for socio-demographic variables and primary and secondary outcomes, including mean (or median) and standard deviation (or range and interquartile range) for continuous variables, and frequency and proportion for categorical variables. At each time point, Chi-square test and two-sample t-test (or Wilcoxon rank sum test if data are skewed) will be used to examine the differences in outcome measures between intervention and control groups for categorical and continuous variables, respectively. Trend tests or analysis of variance (ANOVA) will be used to detect within-group differences across the four follow-up visits.

We will also use Generalized Estimating Equation (GEE) and Generalized Linear Mixed Models (GLMM) to evaluate the overall effectiveness of the intervention after adjusting for socio-demographic variables, engagement, and baseline injury events. Both binary outcomes (whether experienced unintentional injury during the study period) and quantitative count outcomes (number of unintentional injury events and injury prevention knowledge score) at the individual level will be analyzed using these models. Zero-inflation models will be used when needed.

Missing values will be imputed using either the Expectation Maximization (EM) algorithm or Markov Chain Monte Carlo, as appropriate for the data. A per-protocol (PP) sensitivity analysis will be conducted to validate ITT results. All statistical analyses will be performed using the up-to-date version of R. All statistical tests will be two-sided, with the level of 0.05 considered statistically significant.

Subgroup analyses will be performed to assess the impact of socio-demographic factors on the intervention effectiveness, including sex and age of children, grade level of preschoolers, education level of preschooler caregivers, and household income per capita in the prior 12 months. Subgroup analyses will follow the same statistical strategies for primary analyses.

This study will be rigorously conducted, analyzed, and reported in accordance with the Standard Protocol Items: Recommendations for Interventional Trials (SPIRIT) 2013 statement [37] and the Consolidated Standards of Reporting Trials (CONSORT) 2010 statement [38].

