**Methods and analysis:**

A single-blinded, 12-month follow-up, parallel-group cluster randomized controlled trial with a 1:1 allocation ratio will be implemented in two selected counties. In total, at least 2378 rural preschoolers aged 3–6 years old will be recruited from 12 preschools, 6 in Yang County and 6 in Shicheng County. Clusters will be randomized at the preschool level and allocated to the control group (routine school-based education) or the intervention group (routine school-based education plus the Safety Experience Room education). External support strategies will be implemented by local partners to minimize attrition. Data collection will be conducted at baseline and then every 3 months during a 12-month follow-up time period. Intention-to-treat (ITT) data analysis will be used. Generalized estimation equations (GEE) will evaluate the effectiveness of the program and generalized cost-effectiveness analysis (GCEA) will evaluate the cost-effectiveness of it. A per-protocol (PP) sensitivity analysis will assess the robustness of ITT results. Subgroup analyses will be performed to evaluate the impact of socio-demographic factors on the intervention effect, following the same strategies as the primary analyses.

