### Sample size

Based on a previous survey [28], we conservatively estimated that unintentional injury incidence among preschoolers aged 3–6 years old in the study sites over a 12-month period will be 30%. According to relevant reports [29], we estimated the effect size of the Safety Experience Room intervention will be 0.75 (incidence rate ratio) compared with a traditional educational intervention. An intra-class correlation (ICC) of 0.005 within a cluster size of 200 children per preschool was estimated [30, 31]. Nearly whole rural preschoolers stay enrolled in the same preschool throughout childhood, so we conservatively estimate a maximum attrition rate of 10% over the 12-month follow-up time period. Given these estimates, a minimum sample size of 2378 preschoolers is sufficient to achieve statistical power of 80% at the significance level of 0.05. Our preliminary surveys indicate most local rural preschools have 200 to 300 children, so 12 preschools will be adequate to recruit the needed sample size.

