**Fig. 2 Fig2:**
[figure not shown]
Timeline for participant enrollment, intervention implementation, and assessment

Each invited preschool will receive an official invitation letter along with relevant project materials. To avoid contamination between children within the same preschool, we will randomize the intervention and control programs at the school level. Consequently, 6 preschools will be randomly allocated to the intervention group, including 3 from Yang County and 3 from Shicheng County, while the other 6 preschools will be allocated to the control group, also including 3 from Yang County and 3 from Shicheng County.

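### The per-visit chi-square, t and Wilcoxon comparisons between arms ignore preschool clustering, which the sample size allows for; their true error rate is about 8–10% for a quarterly injury result and 15–21% if applied to the 12-month outcome

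*Protocol article*

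**What the plan says.** The unit of randomisation is the preschool: "we will randomize the intervention and control programs at the school level" (Preschool recruitment, text after Fig. 2), with six preschools per arm, three from each county.

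The Sample size section allows for this: "An intra-class correlation (ICC) of 0.005 within a cluster size of 200 children per preschool was estimated".

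The Data analysis plan then lists the outcome analyses in this order:

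- Between arms: "At each time point, Chi-square test and two-sample t-test (or Wilcoxon rank sum test if data are skewed) will be used". No adjustment for preschool is mentioned.
- Within arms: "Trend tests or analysis of variance (ANOVA) will be used to detect within-group differences across the four follow-up visits".
- Models: "We will also use Generalized Estimating Equation (GEE) and Generalized Linear Mixed Models (GLMM) to evaluate the overall effectiveness of the intervention". These cover the binary injury outcome over the study period, the injury count and the knowledge score. The abstract also assigns effectiveness to the model: "Generalized estimation equations (GEE) will evaluate the effectiveness of the program".
- Subgroups: "Subgroup analyses will follow the same statistical strategies for primary analyses".

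One level covers everything: "All statistical tests will be two-sided, with the level of 0.05 considered statistically significant". The section does not call the simple tests descriptive and does not rank them against the models.

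**The concern.** The design and the first-named outcome tests disagree. The sample size treats children in one preschool as correlated and nearly doubles the number recruited for that reason. The chi-square, t and Wilcoxon tests treat the same children as independent, so their standard errors are too small and their p-values too favourable. Because they are read at 0.05 with no stated hierarchy, a per-visit result can be reported as significant while the cluster-aware model does not support it.

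The within-group tests have a different fault. The same children are surveyed at all four follow-ups, so the visits are not independent groups. Change within one arm also does not estimate the randomised contrast, whichever way the test errs.

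**Working it through.** **1. The plan's own figure.** Inputs from the Sample size section: 30% incidence over 12 months, ratio 0.75 (so 22.5%), ICC 0.005, 200 per preschool, 10% attrition, 80% power, two-sided 0.05.

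- Unpooled two-proportion formula: n = (1.960 + 0.842)² × (0.30×0.70 + 0.225×0.775) / 0.075² = 536.3 per arm.
- Design effect: 1 + (200 − 1) × 0.005 = 1.995.
- Total: 2 × 536.3 × 1.995 / 0.9 = 2377.8, i.e. the stated 2378.

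Without the design effect the total would be 2 × 536.3 / 0.9 = 1192. The clustering allowance is therefore inside the stated number.

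**2. Size of an unadjusted test on the 12-month outcome.** With DE = 1 + (m − 1) × 0.005, a nominal 5% test has size 2 × [1 − Φ(1.96/√DE)]. The lowest m is 2378 × 0.9 / 12 = 178 analysed children per preschool. The others span the 200 to 300 children that the plan reports for most local preschools.

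| m | DE | Size by formula | Simulated chi-square |
|---|---|---|---|
| 178 | 1.885 | 15.3% | 15.4% |
| 200 | 1.995 | 16.5% | 16.5% |
| 250 | 2.245 | 19.1% | 19.0% |
| 300 | 2.495 | 21.5% | 21.2% |

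The simulation is beta-binomial, 6 against 6 clusters at 30%, 40,000 runs. A continuity correction lowers the simulated range only to 14.3%–20.4%.

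**3. Size at one quarterly visit.** The quoted tests are per time point, and the plan gives no quarterly ICC. Assume that the 30% accrues evenly and that each preschool's hazard is stable over the year.

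- Quarterly risk: 1 − 0.70^(1/4) = 0.0853.
- Between-preschool variance of the 12-month risk: 0.005 × 0.30 × 0.70 = 0.00105. On the cumulative-hazard scale: 0.00105 / 0.70² = 0.00214.
- Variance of the quarterly risk: 0.00214 / 16 × 0.9147² = 0.000112.
- Quarterly ICC: 0.000112 / (0.0853 × 0.9147) = 0.0014.

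The same size formula then gives 8.0% at 178, 8.4% at 200, 9.3% at 250 and 10.1% at 300. Simulation with gamma-distributed preschool hazards agrees (about 8% to 10%). It gives 27% to 32% for at least one false positive over four visits. Four independent, valid 5% tests would already give 1 − 0.95⁴ = 18.5%.

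**4. Knowledge scores.** No ICC is stated. For scale only, at 200 per preschool an ICC of 0.01 would give 26% and 0.05 would give 55%. Both ICCs are assumptions.

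**5. Within-group ANOVA over four visits.** A stable preschool effect cancels when visits are compared. With 1200 children per group and ICC 0.005, the simulated size under the null is 5.2% with almost no within-child correlation, 2.8% at a correlation of 0.1 and 1.4% at 0.3 (correlations assumed). It rises to about 25% only if a preschool-by-visit variance share of 0.005 is added, a quantity the plan does not give.

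**The case against.** The strongest reply is that effectiveness inference is already model-based. The abstract names GEE, and the Data analysis plan gives overall effectiveness to GEE and GLMM. The simple tests follow the descriptive statistics, and being listed first does not make them primary. This stands: a reader might infer that the trial's main conclusion rests on unadjusted tests, and the document does not say so. What remains is that these tests are committed to, read at 0.05 and not labelled descriptive.

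Three further inferences are tempting and not supported:

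- *That every per-visit test, and the ANOVA, runs at 15–21%.* The stated ICC belongs to the 12-month incidence. A quarterly outcome is rarer and, under the assumptions above, has a smaller ICC. The ANOVA tends to be conservative.
- *That about half of such trials would show a false positive at some visit.* This takes 1 − (1 − 0.165)⁴ = 51%, which uses the 12-month error rate at every visit and treats visits as independent. The quarterly calculation gives 27–32%, part of it ordinary multiplicity.
- *That subgroups will be judged by separate tests in each stratum.* The text only says that they follow the primary strategies. Those include GEE and GLMM, and an interaction term is not excluded. A condensed article may leave that to the analysis plan.

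It is also fair to say that allocation is balanced by county, so any part of the ICC due to county would reduce the inflation somewhat.

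**Conclusion.** The point holds for the between-arm chi-square, t and Wilcoxon tests. They ignore clustering that the plan itself quantifies, and they are anti-conservative. The size is about 15–21% if such a test is applied to the 12-month injury outcome, at ICC 0.005 and 178 to 300 children per preschool. For one quarterly injury comparison it is about 8–10%, conditional on even accrual and a stable preschool effect. For knowledge scores it cannot be stated.

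The within-group tests are unsuitable for another reason: they treat repeated measures as independent and do not address the randomised comparison. Since GEE and GLMM are already named for overall effectiveness, this is a should-fix matter and not a defect in the main analysis.

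**What to change.** - Present per-visit outcomes by arm descriptively, and remove the unadjusted chi-square, t and Wilcoxon tests of outcomes between arms.
- Remove the within-group trend and ANOVA tests of outcomes.
- Take all between-arm inference from the GEE/GLMM, naming preschool as the cluster. If visit-specific effects are wanted, obtain them as arm-by-visit estimates from that model.
- As a secondary point, state that subgroup differences are assessed by an arm-by-factor interaction in the same model, reported with its confidence interval.

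The cost is a change of wording before analysis. Per-visit p-values will be less favourable than the unadjusted ones, with standard errors larger by √DE: about 1.12 to 1.20 for a quarterly injury result under the assumptions above, and 1.37 to 1.58 for the 12-month outcome. The sample size has already allowed for clustering in the 12-month outcome at 200 children per preschool.

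### The only stated test of change over the four quarterly visits is made within each arm, where it cannot tell a programme effect from season, ageing or the end of teaching; an arm-by-visit term should replace it

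*Protocol article*

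**What the plan says.** Under Data analysis plan, the protocol article sets out four relevant things.

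- **Within each arm, across visits:** "Trend tests or analysis of variance (ANOVA) will be used to detect within-group differences across the four follow-up visits".
- **Between arms, at each visit:** in the sentence just before, chi-square and two-sample t-tests (Wilcoxon if skewed) "will be used to examine the differences in outcome measures between intervention and control groups for categorical and continuous variables, respectively".
- **Effectiveness:** GEE and GLMM are used "to evaluate the overall effectiveness of the intervention after adjusting for socio-demographic variables, engagement, and baseline injury events". The binary outcome for these models is any injury during the study period. No arm-by-visit term is named.
- **Significance:** "All statistical tests will be two-sided, with the level of 0.05 considered statistically significant". Nothing marks the within-group tests as descriptive.

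Under Formal data collection, injury data for both arms "will be collected at baseline and every 3 months throughout the 12-month follow-up time period". Under Interventions, one six-week round of lessons is followed by a repeat: "we will expose the children to a similar set of lessons a second time, over the next six weeks". Teaching therefore lasts about 12 weeks of a 12-month follow-up. Under Primary outcome measure, the four follow-ups are combined into a single 12-month incidence.

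**The concern.** The trial has a concurrent randomised control arm observed at the same visits. Any seasonal pattern, ageing effect or school-calendar effect common to both arms cancels when the arms are compared. A test within one arm gives up that protection. The four visits fall in different seasons, the children are a year older at the end, and teaching takes up only part of the year. A fall or rise across visits in the intervention arm could come from any of these. Correct standard errors would not help, because the difficulty lies in what is being compared.

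Finding significance in one arm and not in the other is no better. It is not a test of whether the arms differ, and it arises often when they do not.

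The stake is limited but real. The Discussion ties a favourable result to wide dissemination in rural China. A significant downward trend among intervention children could be misread as a growing effect, and a significant rise as a waning one.

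**Working it through.** **1. The plan's own figure, to fix the arm size.** Inputs from Sample size: 12-month incidence 30%, ratio 0.75 (hence 22.5%), ICC 0.005, 200 children per preschool, 10% attrition, 80% power, two-sided 0.05.

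- Per arm: (1.960 + 0.842)² × [0.30×0.70 + 0.225×0.775] / 0.075² = 536.3
- Design effect: 1 + 199×0.005 = 1.995
- Total: 2 × 536.3 × 1.995 = 2140.0; divided by 0.9 = 2377.8, rounded up to 2378

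The stated 2378 is reproduced. Completers per arm: 2378 × 0.9 / 2 = 1070.

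**2. Quarterly risk.** A 30% annual risk spread evenly gives q = 1 − 0.70^(1/4) = 0.0853.

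**3. Within-arm tests when there is no programme effect.** The documents give no seasonal or ageing figure, so the size of the swing r is an assumption. Quarterly risk is q(1 + r·c), the same in both arms. Two shapes are used: peak-trough, c = (1, 0, −1, 0), and monotone, c = (1, 1/3, −1/3, −1). Quarters are taken as independent within a child, given the preschool.

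- Trend test, with scores x = (−1.5, −0.5, 0.5, 1.5): expected z = r·|Σxc|·n·q / √[5·n·q(1−q)], where |Σxc| is 2.00 (peak-trough) or 3.33 (monotone)
- Four-visit omnibus test (3 df): noncentrality = r²·Σc²·n·q/(1−q), where n·q/(1−q) = 99.8 and Σc² is 2.00 or 2.22

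Example: peak-trough, r = 0.10. Trend z = 0.20 × 1070 × 0.0853 / √(5 × 1070 × 0.0853 × 0.9147) = 18.26/20.43 = 0.89, which rejects in about 15%. Omnibus noncentrality = 0.01 × 2 × 99.8 = 2.0, which rejects in about 19%.

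| Swing r | Trend, peak-trough to monotone | Omnibus, peak-trough to monotone |
|---|---|---|
| 0 | 5% | 5% |
| 5% | 7–12% | 8–9% |
| 10% | 15–32% | 19–21% |
| 20% | 43–85% | 65–70% |
| 30% | 76–99% | 96–98% |

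A simulation of two arms of six preschools with ICC 0.005 (4000 runs) agrees. For the peak-trough shape at 10/20/30% it gives trend 15/44/75% and omnibus 19/66/96%. For a straight fall of 10/20/30/40% from the first to the fourth quarter, the trend test rejects in 12/35/68/91%.

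**4. Significant in exactly one arm.** From the same simulation (trend test, peak-trough), this is 2 × (rate per arm − rate in both):

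- flat: 2 × (0.051 − 0.003) = 10%
- r = 10%: 2 × (0.148 − 0.0215) = 25%
- r = 20%: 2 × (0.437 − 0.187) = 50%
- r = 30%: 2 × (0.755 − 0.568) = 37%

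**5. Arm-by-visit test (3 df), same runs.** It rejects in 4.3% to 5.3% in every scenario.

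**6. The per-visit arm comparisons.** If the stated ICC also held for quarterly outcomes (an assumption), a test that ignores clustering compares 1.96/√1.995 = 1.39 with the normal curve. The true error is then about 17% against a nominal 5%.

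**7. Power of the interaction.** Suppose the quarterly risk ratio is 0.75 in three quarters and 1.00 in the fourth. The log odds ratio is −0.311 (variance 0.0276 per quarter) for three quarters, and 0 (variance 0.0240) for the fourth. Weights are 3/0.0276 = 108.8 and 1/0.0240 = 41.7. The noncentrality is 0.311² × 108.8 × 41.7/150.5 = 2.9, giving power of about 27% on 3 df.

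**The case against.** The strongest reply is that nothing of consequence rests on these tests. Effectiveness is assigned to the between-arm GEE/GLMM, the primary outcome is one 12-month incidence, and the cost-effectiveness analysis uses the between-arm difference over 12 months. The article nowhere says that a within-group trend will be read as a programme effect. All of this stands, and it confines the point to a supplementary analysis.

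Three stronger readings are tempting, and the documents do not support them.

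- *The randomised comparison by quarter is not made, so persistence of effect is left unanswered.* The article does compare the arms at each time point, and those contrasts cancel shared season and ageing. They are unadjusted for preschool and do not test change in effect, but they exist. The article also sets no durability objective; it justifies quarterly visits by recall bias.
- *Spurious trends will appear.* That depends on a seasonal or ageing swing that the documents do not give. If risk is flat, the rate is 5%. Moreover, if risk truly varies by quarter, rejecting no difference across visits is a correct rejection. The percentages above are power to detect season, and become error rates only if the result is read as evidence about the programme.
- *The first quarter is the teaching quarter.* Two six-week rounds suggest it, but Table 1 says only that the lessons are given twice in one semester, the section on secondary outcomes refers to a 12-month intervention period, and the timeline figure is not available here. The alignment of lessons with quarters is not established.

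A fuller analysis plan may contain an arm-by-visit term. Its absence from an article is not the complaint. The complaint is that the article commits to a test that is the wrong tool, and adding a term elsewhere would not withdraw it.

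**Conclusion.** The point holds as a modest criticism of a secondary analysis. The stated within-group tests carry no information about the programme, whatever their p-values, and that conclusion needs no assumed figure. The rejection range of roughly 15% to 99% rests on an assumed shared swing of 10% to 30%, 1070 completers per arm, and quarters independent within a child given the preschool. At a 5% swing the range is only about 7% to 12%. The primary 12-month comparison and the sample size are untouched. The change is worth making, but the trial's main conclusion does not depend on it.

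**What to change.** Remove the within-group trend and ANOVA tests, and show within-arm quarterly injury rates descriptively, without p-values. In their place, fit the planned GEE or GLMM to the four quarterly outcomes, accounting for both preschool and repeated reports on the same child, with visit (categorical), arm and arm-by-visit. Report the arm ratio with its confidence interval at each visit; this also supersedes the unclustered per-visit tests. Test the interaction as a secondary analysis. Group quarters as during or after teaching according to the actual lesson calendar, fixed before unblinding.

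The cost is a change of wording in the analysis plan, with the same data and the same family of models. The drawback is power: as shown above, even an effect that disappears entirely in the last quarter would be detected only about a quarter of the time. A non-significant interaction must not be reported as proof that the effect is constant; the per-visit ratios and their intervals should carry the interpretation.
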